# Neuroplasticity induced by general anaesthesia: study protocol for a randomised cross-over clinical trial exploring the effects of sevoflurane and propofol on the brain – A 3-T magnetic resonance imaging study of healthy volunteers

**DOI:** 10.1186/s13063-020-04468-y

**Published:** 2020-09-22

**Keywords:** Neuroplasticity, Neuroplastic changes, General anaesthesia, Magnetic resonance imaging, Sevoflurane, Propofol, Healthy volunteers, Consciousness, Cognitive, Fatigue

## Abstract

**Background:**

Although used extensively worldwide, the effects of general anaesthesia on the human brain remain largely elusive. Moreover, general anaesthesia may contribute to serious conditions or adverse events such as postoperative cognitive dysfunction and delirium. To understand the basic mechanisms of general anaesthesia, this project aims to study and compare possible de novo neuroplastic changes induced by two commonly used types of general anaesthesia, i.e. inhalation anaesthesia by sevoflurane and intravenously administered anaesthesia by propofol. In addition, we wish to to explore possible associations between neuroplastic changes, neuropsychological adverse effects and subjective changes in fatigue and well-being.

**Methods:**

This is a randomised, participant- and assessor-blinded, cross-over clinical trial. Thirty healthy volunteers (male:female ratio 1:1) will be randomised to general anaesthesia by either sevoflurane or propofol. Multimodal magnetic resonance imaging (MRI) of the brain will be performed before and after general anaesthesia and repeated after 1 and 8 days. Each magnetic resonance imaging session will be accompanied by cognitive testing and questionnaires on fatigue and well-being. After a wash-out period of 4 weeks, the volunteers will receive the other type of anaesthetic (sevoflurane or propofol), followed by the same series of tests. Primary outcomes: changes in T1-weighted 3D anatomy and diffusion tensor imaging. Secondary outcomes: changes in resting-state functional magnetic resonance imaging, fatigue, well-being, cognitive function, correlations between magnetic resonance imaging findings and the clinical outcomes (questionnaires and cognitive function). Exploratory outcomes: changes in cerebral perfusion and oxygen metabolism, lactate, and response to visual stimuli.

**Discussion:**

To the best of our knowledge, this is the most extensive and advanced series of studies with head-to-head comparison of two widely used methods for general anaesthesia. Recruitment was initiated in September 2019.

**Trial registration:**

Approved by the Research Ethics Committee in the Capital Region of Denmark, ref. H-18028925 (6 September 2018). EudraCT and Danish Medicines Agency: 2018-001252-35 (23 March 2018). www.clinicaltrials.gov, ID: NCT04125121. Retrospectively registered on 10 October 2019.

## Background

General anaesthesia (GA) was introduced successfully more than 150 years ago, and has been a prerequisite for the advancement of modern surgery [1]. Globally, approximately a quarter of a billion major surgeries, and a possibly higher number of less invasive procedures and examinations, require GA every year. In Denmark alone, approximately 200,000 patients annually undergo GA [2]. Although used extensively on a daily basis all over the world, the effects of GA on the human brain remain largely elusive.

### General anaesthesia

Presently, the two main types of GA are: (1) inhalation anaesthesia by a volatile agent, and (2) total intravenous anaesthesia (TIVA). For inhalation anaesthesia, typically a halogenated anaesthetic gas, such as sevoflurane, is administered. To alleviate pain during surgical procedures, an intravenously administered (IV) analgesic is commonly administered (e.g. fast-acting opioids such as remifentanil). For TIVA, both the hypnotic agent and any supplemental analgesics are administered intravenously. Propofol is the most widely used fast-acting hypnotic agent for GA by TIVA. Early studies on the action of anaesthetics have focussed mainly on their molecular and cellular targets. There is consensus that inhaled anaesthetics induce anaesthesia by enhancing inhibitory and attenuating excitatory ion channels in cell membranes. However, the precise mechanism of action, and whether this occurs through direct binding or by physical changes of membranes, is not known [3]. By contrast, propofol appears to activate the inhibitory pathway of the neurotransmitter gamma-aminobutyric acid (GABA) through receptors located predominantly in the parietal cortex and thalamus [4–6]. The hypnotic effect may be caused by interaction with other neurotransmitters [6]. The effect of GA is dose-dependent. Initially, working memory is suppressed. As the dose is increased, consciousness and voluntary responsiveness begin to fade, while some autonomic processes remain operational until very high doses are reached [7–9]. It is well-known that GA does not induce unconsciousness simply by a widespread, non-specific suppression of neural activity [10]. However, the specific neural mechanisms underlying amnesia and loss of consciousness, including when these phenomena are induced by GA, remain controversial [11–13]. In addition, which method for GA (inhaled anaesthetics vs. TIVA) that should be preferred is a topic of ongoing discussion among anaesthesiologists [14].

### Surgical stress and cognitive effects

The surgical trauma together with GA can elicit profound changes in the endocrine, immune and nervous systems, collectively known as the surgical stress response. The pathophysiology of this stress response is characterised by activation of the hypothalamic-pituitary-adrenal-axis and increased sympatho-adrenomedullary activity. This leads to increased secretion of stress hormones, such as cortisol and pro-inflammatory cytokines, as well as altered autonomic nervous system activity and immune function. While ideal for overcoming physiological stress, hyperactivation may ultimately cause dysfunction of one or more organs including the central nervous system (CNS). The response may manifest as increased pain, disturbances in the circadian rhythms, as well as impairment of memory and executive functions. Post-operative cognitive dysfunction (POCD) is associated with increased mortality and increased risk of leaving employment prematurely [15]. Post-operative delirium (POD) is characterised by fluctuating levels of attention and consciousness. Associated with both longer hospitalisation, poor outcome, and increased early mortality, POD is a serious condition [16, 17]. General anaesthesia alone may also trigger a stress response in the CNS [18]. Both POCD and POD are well-described among older-age patients [19]. A Cochrane review of the clinical studies focussing on older-age non-cardiac surgery patients receiving inhalational vs. IV GA did not find significant difference in the post-operative cognitive status of the two groups [20]. However, very few studies have explored the effects on cognitive performance resulting from GA in younger adults [21–23]. To the best of our knowledge, the isolated effects from GA with inhalation anaesthesia vs. TIVA have never been investigated.

### MRI

Brain imaging has contributed substantially to our current understanding of brain structure and function. Structural magnetic resonance imaging (sMRI) provides information about microstructural changes in brain anatomy [24], while functional MRI (fMRI) permits measurements of neuronal activity during stimulation [25, 26] and at rest (= resting-state fMRI (rsfMRI)) [27]. Moreover, MRI may be used to investigate cerebral haemodynamics and for pharmacological imaging (the interaction between brain physiology, neuronal activity and pharmacological agents). Thus, MRI offers ideal opportunities to study the in vivo effects of GA on the human brain. However, only a very limited number of studies have been published within this field. No studies have examined possible neuroplastic effects of GA on the brain by advanced neuroimaging techniques such as MRI or positron emission tomography (PET). Most of the studies focus on changes in regional cerebral blood flow or neuronal activity during sedation with propofol [28–31]. Mhuircheartaigh et al. found decreasing activity with increasing depth of propofol sedation in areas corresponding to the stimulus applied during propofol sedation: the anterior insula, anterior cingulate cortex and superior temporal gyrus during auditory stimulation, and in the putamen and globus pallidus (contralateral), and insula (bilateral) in response to noxious stimulation on the left hand. Furthermore, they found that propofol sedation impairs the function of basal ganglia circuits and thalamo-cortical connectivity [30]. The same research group described similar findings in another study, including impaired thalamo-cortical networks [31]. Two MRI studies focussed on memory functions during propofol sedation: Quan et al. found inhibited activation of the superior and middle temporal gyri, and inferior parietal lobuli with auditory stimuli [29], and Pryor et al. found suppression of the hippocampal response to visual stimuli [28]. Four studies in which PET scans were performed during propofol sedation suggested impaired thalamocortical connectivity and decreased activity in the cerebellum [32–35]. In addition to these findings, Schlunzen et al. found metabolic and vascular depression in the cortex and thalamus [36]. Thus, propofol sedation in subanaesthetic doses seems to impair the thalamocortical network. Three studies have used fMRI to assess changes in regional cerebral blood flow (CBF) in response to mild sevoflurane sedation [37–39]. One study evaluated CBF during visual, auditory and motor activation, and found a significant decrease in CBF in the primary and secondary visual cortices, thalamus, hippocampus and supplementary motor area with sevoflurane [37]. A comparable study showed similar findings regarding the visual and auditory cortical regions [38]. However, the third study found that sevoflurane increased both regional cerebral blood volume and CBF in the striatum, thalamus and frontal, parietal and occipital cortices [39]. Only a single study utilising resting-state fMRI (rsfMRI) has evaluated sevoflurane in doses equalling clinical GA, and found a general reduction in functional connectivity maps (motor cortices) of 78–98% compared to the awake state [40]. Thus, sedation with sevoflurane in subanaesthetic doses may alter the cerebral haemodynamics, whereas GA with sevoflurane (in higher doses) seems to impair cortical connectivity. However, the research in this area remains very limited. As for comparing GA with sevoflurane vs. propofol, a small PET study with eight volunteers found a comparable overall reduction in CBF and oxygen metabolism for both types of anaesthesia, with a slightly less pronounced effect of sevoflurane [41].

Overall, these explorative functional studies were conducted using varying levels of sedation and included very small sample sizes. The stimulation and chosen cerebral regions of interest varied greatly. While they do suggest that pharmachological sedation might be associated with a reduction in the thalamocortical network, they are hardly comparable or collectively conclusive regarding GA in clinically relevant doses. Importantly, possible structural changes in the brain induced by GA remain unexplored.

In this present study, we want to focus on the effects of the two main anaesthetic agents used for GA in healthy volunteers, without the interactions and confounders of polypharmacy frequently found in patients scheduled for GA on clinical indications. Multimodal imaging by MRI will be used to study the structural and functional effects of the anaesthetic agents on the brain. In addition, neuropsychological testing will be performed to assess the impact on cognitive performance resulting from the anaesthetic agents. Furthermore, we will use questionnaires to measure changes in self-reported fatigue and general well-being following GA. Thus, the effects induced by isolated exposure to GA by sevoflurane vs. propofol can be explored and described.

### Aim

To explore and compare possible de novo neuroplastic changes induced by GA with a volatile agent (sevoflurane) and TIVA (propofol), respectivelyTo elucidate possible associations between MRI findings and clinical outcomes

### Hypotheses

The hypotheses of this study are that:
Compared with baseline, GA by propofol or sevoflurane is associated with (a) focal micro-structural neuroplastic changes (volume and morphology), (b) changes in white-matter tracts and (c) changes in resting- state neuronal connectivity, as detected by MRIGeneral anaesthesia by sevoflurane is associated with more pronounced changes in neuroplasticity compared with GA by propofolCompared with baseline, GA using propofol or sevoflurane is associated with reduced self-rated well-being (increased fatigue and reduced general comfort) and executive cognitive functions; a more pronounced reduction is observed after sevoflurane compared with propofolThe presence and severity of structural MRI changes after GA are correlated to changes in cognitive performance as well as self-rated measures of fatigue and well-being

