**Total score ≥ 4 predicts difficult intubation**			

### Outcomes

Outcome parameters will be measured before and after GA, and subsequently after 1 and 8 days. Possible differences can, thus, be assessed before and after GA, within each type of general anaesthesia, and between GA methods (sevoflurane vs. propofol).

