#### Secondary outcomes

Differences in resting-state functional MRI (rsfMRI)Severity and characteristics of fatigue, as measured by Multidimensional Fatigue Inventory (MFI-20) [42]Cognitive function including attention, speed, and executive functions as measured by computer-based neuropsychological tests (Paced Auditory Serial Addition Test (PASAT), Test of Attentional Performance (TAP) and Conners Continuous Performance Test, 3rd edition (CPT3))Quality of Recovery – 15-item questionnaire (QoR) [43]Correlations between MRI findings as well as clinical outcomes as described above

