#### Intervention day (day 0): pre-intervention procedure

The volunteer will be re-screened according to all inclusion and exclusion criteria. It will be ensured that the volunteer is fasting according to the recommendations of The Danish Society for Anaesthesia and Intensive Care Medicine (DASAIM), which are aligned with the guidelines from the European Society of Anaesthesiologists [45]; thus, 2 h of fasting are required for clear liquids and 6 h for all other oral intake. After changing into hospital clothing, baseline MRI scans will be performed (MRI 1). Cognitive testing will be performed, and the questionnaires MFI-20 and QoR will be filled out by the volunteer.

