##### Post-intervention care

In the post-operative care unit, the volunteer will be continuously monitored with heart rate and SpO_2_, while blood pressure will be measured every 15 min. The volunteer will receive oxygen supplementation if needed. Monitoring, care, discharge and intake of food and drinks will adhere to DASAIM’s standard of post-operative care [49, 50]. The volunteers will be observed for at least 2 h. Then, cognitive testing and questionnaires will be repeated before MRI 2. After MRI 2 the volunteer will be allowed to leave the hospital, but will be instructed not to remain alone for the next 24 h as recommended by the American Society of Anaesthesiologists (ASA) [51].

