##### Follow-up MRI scan day (+ 8 days)

Eight days (7–10) after GA cognitive testing, questionnaires and MRI scans (MRI 4) will be repeated once more.

### Study session 2

Study session 2 will be initiated no earlier than 4 weeks after study session 1 (4 weeks after the intervention day), to ensure a sufficient wash-out period. Before the initiation of study session 2, the volunteer will be re-screened to ensure eligibility for continued participation. Session 2 will be identical to session 1, except that general anaesthetic will be changed from propofol to sevoflurane or vice versa.

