### Statistical analysis

The distribution of continuous data is rated for normality using residual-plot or by the Shapiro-Wilk W test. Normality can be reached by simple transformation (log, logit). Statistical comparison of paired data is performed with parametric or non-parametric method or by analysis of variance (ANOVA). Depending on the distribution, testing is performed with Mann-Whitney or Wilcoxon tests, respectively. The risk for Type I errors is reduced by reducing the significance level to 0.05 (alpha). A general summation goal will be used to avoid mass-significance by repeated measurements. In statistical measurements where multiple comparisons cannot be avoided, Duncan’s corrections (i.e. secondary outcome parameters) are performed. For MRI data, correction for multiple comparisons is performed with Bonferroni’s correction or the false discovery rate (FDR). For statistical comparison between categorical variables (i.e. psychometric data) the *X*^2^ test with Yates’ correction is performed.

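### Change in cognitive score from the session baseline mixes anaesthetic effect with practice gain, so a real decline in executive function can be masked

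*Protocol article*

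**What the plan says.** All places are in the protocol article.

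- **Hypotheses (third hypothesis).** The comparator in the first clause is baseline: "GA using propofol or sevoflurane is associated with reduced self-rated well-being (increased fatigue and reduced general comfort) and executive cognitive functions". A separate second clause expects a larger reduction after sevoflurane than after propofol.
- **Background, MRI.** The purpose is put causally: "neuropsychological testing will be performed to assess the impact on cognitive performance resulting from the anaesthetic agents".
- **Secondary outcomes.** The outcome is "Cognitive function including attention, speed, and executive functions as measured by computer-based neuropsychological tests", namely PASAT, TAP and CPT3.
- **Outcomes.** "Outcome parameters will be measured before and after GA, and subsequently after 1 and 8 days".
- **Intervention day, pre-intervention procedure.** Baseline sitting: "Cognitive testing will be performed, and the questionnaires MFI-20 and QoR will be filled out by the volunteer".
- **Post-intervention care.** Same-day sitting, after at least 2 h of observation: "Then, cognitive testing and questionnaires will be repeated before MRI 2". The two follow-up sections add sittings at 1 day and at 8 (7 to 10) days.
- **Study session 2.** "Session 2 will be identical to session 1, except that general anaesthetic will be changed from propofol to sevoflurane or vice versa".
- **Study design and Sample size.** Each volunteer receives both anaesthetics and acts as their own control. No session or group is without anaesthesia.
- **Randomisation and blinding.** The questionnaires and cognitive tests are shown to volunteers before randomisation. The article does not say whether this includes a practice run.
- **Statistical analysis.** Paired data are compared by a parametric or non-parametric method or by ANOVA.

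**The concern.** A volunteer who sits the same attention, speed and working-memory tests again after a few hours, a day and a week may do better simply because the tasks are familiar. That gain runs opposite to the hypothesised reduction. If there is a gain, a finding of no change from baseline is not evidence that anaesthesia left executive function intact, because an impairment and a practice gain of similar size cancel.

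This matters because the first clause of the third hypothesis is a claim about each agent against baseline, and the Background reads the test results as caused by the agents. The Dissemination section commits to publishing negative results, and the Background notes how few studies have looked at cognition after anaesthesia in younger adults. A masked decline would enter that thin literature as no impairment.

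The point concerns the cognitive tests only. MFI-20 and QoR-15 belong to the same hypothesis but are self-ratings, not tests of ability.

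**Working it through.** **1. Number of sittings.** Before anaesthesia, after it, at 1 day and at 8 days gives 4 per session. Two sessions give 4 × 2 = 8.

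**2. What the baseline comparison estimates.** Orient scores so that higher is better. At post-anaesthesia occasion *k* of session *p*, for agent *a*:

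mean change from session baseline = θ(*a*,*k*) + g(*p*,*k*)

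Here θ is the anaesthetic effect and g the gain from repetition. Anaesthesia falls between the first and second sitting of both sessions, so no occasion shows g without θ. A null of zero change is θ + g = 0, not θ = 0.

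**3. Whether a model on all eight sittings could separate them.** Take eight free occasion effects (an 8 × 8 identity, rank 8) and add a post-anaesthesia indicator (0,1,1,1,0,1,1,1). That indicator is the sum of six of the existing columns, so the rank stays 8. The average anaesthetic effect is not estimable unless a shape is assumed for the practice curve.

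**4. Size of the masking.** The article gives no power figure for cognition. Its 30 volunteers come from the grey-matter calculation (8% difference, SD 10%, alpha 0.025, 80% power): 2 × 10² × (2.241 + 0.842)² / 8² = 29.7, rounded up to 30. That figure reproduces, but it enters here only as n.

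Inputs:
- n = 30 completers (Study design).
- Alpha 0.05 (Statistical analysis), taken as two-sided, as in Sample size.
- True decline 0.5 SD of the paired difference (assumed; with n = 30 a paired t-test has 80% power at about 0.53 SD).
- Practice gain g from 0 to 0.5 SD of the paired difference (assumed range).

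The paired t-test has 29 degrees of freedom and critical value 2.045. The noncentrality is (g − 0.5) × √30, and power is the noncentral-t probability below −2.045.

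| Assumed gain g (SD) | Net change (SD) | Noncentrality | Power to show the decline |
|---|---|---|---|
| 0 | −0.5 | −2.74 | 75% |
| 0.1 | −0.4 | −2.19 | 56% |
| 0.2 | −0.3 | −1.64 | 36% |
| 0.3 | −0.2 | −1.10 | 18% |
| 0.5 | 0 | 0 | 2.5% |

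**5. Direction of any false positive.** With no anaesthetic effect, the noncentrality is g × √30.

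| g (SD) | Significant decline | Significant improvement |
|---|---|---|
| 0 | 2.5% | 2.5% |
| 0.2 | 0.13% | 18% |
| 0.3 | 0.02% | 36% |

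Practice makes a false decline rarer. The extra rejections are improvements.

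**6. The between-agent contrast.** Let δ be the sevoflurane effect minus the propofol effect at a given occasion, and let g1 and g2 be the gains at that occasion in sessions 1 and 2. The mean within-person difference (sevoflurane minus propofol) is δ + (g1 − g2) when sevoflurane comes first and δ − (g1 − g2) when propofol comes first. The average of the two sequence means is δ, which is what a model with a period term estimates. In a simulation with gains of 0.5 SD in session 1 and 0.2 SD in session 2, and no agent effect, this contrast rejected in 5.3% of runs.

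Without a period term the bias is (n1 − n2)/n × (g1 − g2), where n1 and n2 are the numbers in the two orders. Order is set by simple randomisation, so a split of 12:18 or more uneven has probability 36%. A 12:18 split leaves 6/30 = 20% of the session difference in the contrast.

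**The case against.** **The size rests on assumption.** The article gives no practice effect, retest reliability or SD for any of the three tests, so the power figures are conditional on a range. This stands. That the two effects cannot be separated within an agent does not depend on the range.

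**Details may sit in the full protocol or analysis plan.** Parallel forms, warm-up trials and model terms are often left out of an article, the early presentation of the tests may be familiarisation, and no particular paired test is fixed. All of this could reduce the gain, and none of it is counted here as an omission. But the claim against baseline and the absence of an anaesthesia-free session are stated in the article, and step 3 shows that an analysis plan cannot undo them from the trial data without an assumed practice curve.

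**Cognition is secondary and the aim is exploratory.** This is right, and it limits the weight of the point. It is still a named, directional hypothesis.

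**Two stronger readings are tempting and are not supported.** A reader might infer that practice would also yield false evidence of impairment. It would not: the hypothesis predicts a reduction, and step 5 shows that practice makes a significant decline less likely. A reader might also infer that practice spoils the correlations between MRI change and cognitive change in the fourth hypothesis. A gain common to all volunteers leaves a correlation unchanged. Only variation in gain between people, or pooling sessions with different mean gains, could matter, and the documents give no basis for either.

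**Conclusion.** The point holds for the baseline clause of the third hypothesis, for the cognitive tests only. The design cannot tell anaesthetic effect from practice within an agent, and the likely error is to report no impairment when there is some. For a true 0.5-SD decline, power falls by about 19 points at a gain of 0.1 SD (75% to 56%) and by about 39 points at 0.2 SD (75% to 36%). At 0.5 SD the decline is cancelled.

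This assumes 30 complete pairs, a paired t-test at two-sided 0.05, practice that improves scores, and gains in the assumed range. The second clause, sevoflurane against propofol, is sound if period is modelled, if the first session leaves no carry-over and if the practice gain does not depend on the agent. The point is worth correcting because it changes what the trial may conclude, but it does not touch the primary MRI outcomes.

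**What to change.** For the cognitive tests:

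1. Base the conclusion on the sevoflurane-propofol contrast of within-session change from baseline, at matched test occasions, in a model with a period term.
2. Report the within-agent results as change on repeated testing.
3. State in advance that neither a fall from baseline nor its absence is read as the effect of anaesthesia. A fall would be net of an unknown gain, and no change could be a cancelled decline.
4. Do not present a model of all eight sittings, or practice-adjusted change scores, as a correction, since the average anaesthetic effect is not estimable with free occasion effects.
5. If wanted, report the difference between the session-2 baseline (fifth sitting) and the session-1 baseline (first sitting) descriptively, as a sign of retained practice. It assumes no lasting effect of the first anaesthetic, and it does not measure the gain at the same-day, 1-day or 8-day sitting.

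The cost is a change of wording in the third hypothesis and the analysis section and a period term in one analysis of data already scheduled, with no new visits. The downside is a weaker cognitive claim for each agent on its own.
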